### Sample size estimation

As the differential effects of priming iTBS on hemiparetic upper-limb training have yet to be examined, we based our sample-size estimate on existing three-group trials. A recent meta-analysis reported a pooled Cohen's *d* = 0.60 favoring iTBS for upper-limb motor improvement. For a three-group design, this translates to an effect size *f* of ~0.30 (15). *A priori* power analysis (power = 0.80, two-tailed α = 0.05) indicated that 45 participants would be required. Accounting for an anticipated 15% dropout rate, we will recruit 18 participants per group, for a total sample size of 54. This recruitment target is expected to yield at least 45 participants completing the trial.

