### Statistical analysis

For this study, MEP data will be processed and analyzed statistically using the Statistical Package for the Social Sciences (SPSS, version 26.0). For normally distributed continuous data, repeated-measures analysis of variance will be used for intra-group comparisons and independent-samples *t*-test for inter-group comparisons; for non-normal data, Friedman test and Wilcoxon rank-sum test will be adopted; for count data, Pearson χ^2^ test will be employed. The intraclass correlation coefficient (ICC) will be used to assess the inter-rater reliability of MEPs and MAS (17), and Cronbach's α coefficient will be used to test the internal consistency of scales. A *p* value < 0.05 will be considered statistically significant. The measurement of MEPs will follow the guidelines of the International Federation of Clinical Neurophysiology (27), and the FMA-UE will refer to the criteria for clinically important differences (22). To investigate the therapeutic mechanism, we will examine the association between changes in neurophysiological measures and improvements in clinical behavioral outcomes. Specifically, we will calculate the change scores (from baseline to post-intervention) for each participant in MEP amplitude (or cortical silent period) and in the Fugl-Meyer Assessment for Upper Extremity (FMA-UE) scores. We will then use Spearman correlation analysis to determine whether a significant correlation exists between these two change scores. We hypothesize that participants with greater clinical improvement will also exhibit more pronounced beneficial changes in corticospinal excitability.

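### The stated 80% power for 45 participants in total does not reproduce for the planned between-group test, which has about 35% power at the plan's own effect size

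*Protocol article*

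**What the plan says.** The Sample size estimation section takes a pooled Cohen's d of 0.60 from a meta-analysis and states: "For a three-group design, this translates to an effect size" f of about 0.30. At "power = 0.80, two-tailed α = 0.05" the calculation "indicated that 45 participants would be required". The section names neither the test nor any within-subject correlation.

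The 45 is meant as a trial total. The section continues "Accounting for an anticipated 15% dropout rate" and then "we will recruit 18 participants per group, for a total sample size of 54", and it expects at least 45 completers, which is 15 per arm under 1:1:1 allocation.

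For normally distributed outcomes, the Statistical analysis section says that "repeated-measures analysis of variance will be used for intra-group comparisons and independent-samples" t-tests for comparisons between groups. It plans no group-by-time test and no baseline-adjusted model for between-group comparisons.

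**The concern.** The effect size, power, alpha, number of arms and total are all printed, so the claim can be checked from the page. For a between-group comparison, a difference of 0.60 SD usually needs several dozen participants per arm, not 15. The value f = 0.30 is also exactly d/2, the conversion for two groups, although the text presents it as the conversion for three.

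The power statement governs how a null result will be read. A reader who believes the trial had 80% power for 0.60 SD would take a non-significant difference between Group 3 and a single-site arm as fair evidence against dual-site stimulation. If the power of the planned test is well under one half, that reading is not justified.

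**Working it through.** **Inputs.** From Sample size estimation: d = 0.60, f about 0.30, two-tailed alpha 0.05, power 0.80, 45 completers, 54 recruited, 15% dropout. From Study design: three arms, 1:1:1. From Statistical analysis: t-test between groups.

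**1. Dropout step.** 45 / 0.85 = 52.9, rounded up to 53 and then to 54 for equal arms; 54 × 0.85 = 45.9. This step is correct.

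**2. Planned test: two-sample t-test at d = 0.60.** Degrees of freedom are 2n − 2, the noncentrality is d × √(n/2), and power comes from the noncentral t distribution.

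| n per arm | Noncentrality | Critical t | Power |
|---|---|---|---|
| 15 | 0.60 × √7.5 = 1.643 | 2.048 | 35.5% |
| 18 | 0.60 × √9 = 1.800 | 2.032 | 41.7% |
| 44 | 0.60 × √22 = 2.814 | 1.988 | 79.5% |
| 45 | 0.60 × √22.5 = 2.846 | 1.987 | 80.4% |

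The smallest n giving 80% is 45 per arm, or 3 × 45 = 135 completers.

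**3. One-way ANOVA, three groups, f = 0.30.** Degrees of freedom are 2 and N − 3, the noncentrality is f² × N, and power comes from the noncentral F distribution.

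| Total N | Noncentrality | Power |
|---|---|---|
| 45 | 0.09 × 45 = 4.05 | 39.4% |
| 54 | 0.09 × 54 = 4.86 | 46.8% |
| 108 | 0.09 × 108 = 9.72 | 79.2% |
| 111 | 0.09 × 111 = 9.99 | 80.3% |

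With equal arms, 80% needs 111 completers (37 per arm).

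**4. The conversion to f.** With two equal groups, f = d/2 = 0.30. With three equal groups whose largest gap is 0.60 SD, f depends on the middle mean:
- middle mean halfway between the others: f = 0.60 × √(1/6) = 0.245, needing N = 165;
- two means equal and the third 0.60 SD away: f = 0.60 × √2/3 = 0.283, needing N = 126.

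ANOVA power at N = 45 is then 27% to 36%.

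**5. Can any other model give 45?** For a group-by-time interaction at f = 0.30, with m visits and correlation ρ between visits, the noncentrality is f² × N × m/(1 − ρ), assuming sphericity.
- Three visits, ρ = 0.1: 0.09 × 45 × 3/0.9 = 13.5, power 82.9%.
- Two visits, ρ = 0.25: 0.09 × 45 × 2/0.75 = 10.8, power 81.7%.

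A baseline-adjusted comparison at f = 0.30 needs 60 in total at a baseline correlation of 0.7 and 42 at 0.8, so 45 would require a correlation just under 0.8. The article states none of these models or correlations.

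**6. What 54 recruited can do.** The t-test reaches 80% power at about 1.06 SD with 15 per arm and 0.96 SD with 18. The 95% CI half-width for a pairwise difference is 2.048 × √(2/15) = 0.75 SD with 15 per arm.

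**The case against.** The strongest defence is that the calculation may have been for a repeated-measures design. The article names no test, the trial has three assessments, and a standard interaction calculation at f = 0.30 gives just over 80% at 45 with a low correlation. So it cannot be said that no calculation yields 45. That stands. It does not rescue the plan as written, because repeated-measures ANOVA is assigned to comparisons within groups and t-tests to comparisons between them. Nor is an interaction f of 0.30 equivalent to d = 0.60. If Group 3 exceeds both other arms by 0.60 SD after treatment only, the interaction f is about 0.14 with two visits, or 0.13 with three visits and the effect held at follow-up. Power at 45 is then about 25% at ρ = 0.25 and 36% at ρ = 0.5.

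A reader might infer that a per-arm figure was used as the trial total. The match is exact (45 per arm is the t-test answer at d = 0.60), and both the two-tailed alpha and f = d/2 suggest a two-group calculation. The article does not say so, however, and the interaction calculation is another possible origin. It remains an inference.

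A reader might also take 35% to 39% as the trial's true power without qualification. Those figures hold for an unadjusted comparison with 45 completers. They rise to 42% and 47% if all 54 complete, and baseline adjustment would raise them further.

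On f, the text gives only an approximate value, and 0.283 is not far from 0.30. The conversion is a secondary fault: the shortfall is present even if f = 0.30 is accepted.

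Finally, the article already calls its findings preliminary and its sample modest. That is fair, but it does not correct the stated power.

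**Conclusion.** The sample size statement is wrong as written. For the between-group t-test that the article plans, 45 completers give about 35% power at 0.60 SD, not 80%; a one-way ANOVA at the stated f = 0.30 gives about 39%. The required totals would be 135 and 111. These figures assume equal arms, two-sided alpha 0.05 without multiplicity adjustment, normally distributed outcomes and no use of baseline.

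How 45 was obtained cannot be established from the article, and the conclusion does not depend on it. Whether 0.60 SD is a suitable effect for a trial in which every arm has an active site is a separate matter of judgement and forms no part of this finding.

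**What to change.** Keep 54 and rewrite the paragraph. Remove the 80% claim and the conversion to f. State instead that with 15 evaluable participants per arm the planned between-group t-test has about 35% power for 0.60 SD and reaches 80% only for about 1.06 SD (0.96 SD with 18 per arm).

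If a different model was used for sizing, name it, give the assumed correlation and its basis, recalculate, and make that model the planned between-group analysis, so that sizing and analysis agree.

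In either case, report Group 3 minus Group 1 and Group 3 minus Group 2 with 95% confidence intervals, and say in advance that their half-width will be about 0.75 SD at 15 per arm. This fits the article's own objective of producing effect sizes for later trials.

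The cost is one rewritten paragraph and no extra participants under the first option. The downside is that the stated power becomes less favourable.

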### Randomization and blinding

Randomization will be performed using a computer-generated random sequence by an independent statistician who is not involved in participant recruitment or outcome assessment.

Group allocation will be concealed in sequentially numbered, opaque, sealed envelopes, which will be opened by the intervention therapist immediately prior to the first treatment session. Both participants and outcome assessors will be blinded to group allocation. The intervention devices for active and sham stimulation will be identical in appearance and generate similar auditory and tactile sensations. For sham stimulation, the coil will be positioned at an angle that prevents effective peripheral stimulation while maintaining the same sound and vibration as active stimulation. Treating therapists delivering the stimulation will not be involved in outcome assessment or statistical analysis to maintain assessor blinding and minimize bias.

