**Assessment**
MEPs	√	√	√	√
MAS	√	√	√	√
FMA-UE		√	√	√
ARAT		√	√	√
Modified Barthel index		√	√	√

– T1, screening; T0, baseline; T1, post-intervention; T2, 2-week follow-up; MEPs, motor-evoked potentials; MAS, Modified Ashworth Scale; ARAT, action research arm test.

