### Outcome measures

MEPs are compound muscle action potentials recorded from a target muscle after a single-pulse TMS over the primary motor cortex; they provide an objective index of corticospinal excitability and conduction integrity, with excellent test-retest reliability [Intraclass Correlation Coefficient (ICC) = 0.75–0.94, Kendall's tau = 0.81] (17). In this trial, MEPs will be used to quantify corticospinal plasticity before and after the intervention.

Although the pTBS intervention targets the forearm muscles (FCR and ECRL), MEPs were recorded from the abductor pollicis brevis (APB) because it is a standard target muscle in TMS studies, recommended for its consistent and robust MEP responses and well-defined cortical representation in the primary motor cortex (M1) hand area (17). This approach provides a reliable and comparable measure of overall corticospinal excitability.

Briefly, Ag/AgCl surface electrodes will be placed over the abductor pollicis brevis of the paretic limb. A Magstim 200^2^ stimulator with a 70-mm figure-of-eight coil will deliver 0.2-Hz stimuli to the affected-hemisphere M1 hand area while the participant rests. The following metrics will be obtained: (1) resting motor threshold (RMT), defined as the lowest stimulus intensity eliciting ≥ 50 μV MEPs in ≥ 5 of 10 consecutive trials (17); (2) MEP peak-to-peak amplitude (mV) measured at 120%RMT, averaged across 10 artifact-free trials, as a marker of corticospinal excitability; and (3) MEP latency (ms) from stimulus artifact to onset of the first deflection, reflecting central conduction time. All measurements will be performed by the same assessor at baseline, immediately post-intervention, and at the 2-week follow-up to ensure consistency.

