Positive results remain contingent on three unresolved conditions: (1) Technical—can the dual-coil apparatus be miniaturized into a wearable? (2) Physiological—does efficacy depend on residual corticospinal integrity (do absent MEPs preclude benefit)? (3) Economic—does cost-effectiveness outperform botulinum toxin plus therapy in real-world settings (3, 29)? We are collaborating with a manufacturer on a dual-channel pTBS prototype, but the design metric isn't power output, but rather minimizing the “acoustic fingerprint” that undermines blinding. This engineering constraint may prove the study's most commercially relevant byproduct.

Ultimately, this RCT tests whether the W-shaped model's “optimal zone” exists at the individual level (28). Aggregated group means are secondary; single-subject excitability shifts determine the model's survival.

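### The stated between-arm tests ignore baseline MEP status, which the protocol suspects may govern benefit and records before allocation; a prespecified covariate would recover modest power if MEP status is prognostic

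*Protocol article*

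**What the plan says.** Five places in the protocol article bear on this point.

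- **Discussion.** The closing part states that "Positive results remain contingent on three unresolved conditions". The second of the three reads "does efficacy depend on residual corticospinal integrity (do absent MEPs preclude benefit".
- **Inclusion and exclusion criteria.** Neither the text nor Table 2 requires or excludes a recordable MEP, so both kinds of patient can enrol.
- **Timing.** Table 1 ticks MEPs in every column, and its legend reads "T1, screening; T0, baseline; T1, post-intervention; T2, 2-week follow-up; MEPs, motor-evoked potentials"; the first of these is the pre-baseline column. The Outcome measures section mentions baseline but not screening: "All measurements will be performed by the same assessor at baseline, immediately post-intervention, and at the 2-week follow-up to ensure consistency".
- **Randomization and blinding.** The sequence is described as "Randomization will be performed using a computer-generated random sequence by an independent statistician", and the envelope is "opened by the intervention therapist immediately prior to the first treatment session". On either account of the timing, MEP status can be known before allocation is revealed.
- **Statistical analysis.** For normally distributed data the plan is "independent-samples *t*-test for inter-group comparisons"; for non-normal data it is the Wilcoxon rank-sum test. Neither carries a covariate. Apart from being an outcome, MEP data enter only through a Spearman correlation of change scores.

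The Sample size estimation section says "we will recruit 18 participants per group" and works from d = 0.60.

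**The concern.** The sponsor raises MEP absence as a possible bar to benefit and collects the information in time, but the stated comparison between arms makes no use of it. Every arm receives at least one active stimulation. If absent MEPs did limit benefit, outcomes would therefore be expected to differ by MEP status within each arm, and the factor would act as a prognostic variable.

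Two things would follow from leaving it out. Its variance would stay in the error term and lower power. Any chance difference between arms in the MEP-absent share would also pass into the estimated contrast. At 18 per arm neither is negligible if the factor is strong. The open question in the Discussion would also have no stated analysis by MEP presence.

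**Working it through.** **Inputs from the article:** 18 per arm; d = 0.60; two-sided α = 0.05.

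**Inputs assumed, because the article gives neither:** the MEP-absent share p (20–50%), and the effect b of MEP status on the outcome (0, 0.5, 0.8 or 1.2 within-stratum SD).

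**1. Chance imbalance between two given arms.** The number without an MEP in each arm is Binomial(18, p). The SD of the difference in shares is √(2p(1−p)/18).
- p = 0.2: √(0.32/18) = 0.133
- p = 0.5: √(0.50/18) = 0.167

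A gap of at least 20 points means at least 4 participants, since 3/18 = 16.7 and 4/18 = 22.2 points.

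| MEP-absent share | P(gap ≥ 20 points), one pair | P(gap ≥ 20 points), any of three pairs |
|---|---|---|
| 20% | 0.14 | 0.30 |
| 30% | 0.20 | 0.41 |
| 40% | 0.23 | 0.46 |
| 50% | 0.24 | 0.47 |

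These figures treat MEP status as independent of allocation. They would be lower if the list were stratified by it.

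**2. What such a gap does to the contrast.** Shift = gap × b. At b = 0.8 SD, a 20-point gap gives 0.20 × 0.8 = 0.16 SD, which is 0.16/0.60 = 27% of the design effect. To produce the whole 0.60 SD the gap would have to be 0.60/0.8 = 75 points, more than 4 SDs of the difference. At b = 1.2 SD it would have to be 0.60/1.2 = 50 points, or 3 SDs at p = 0.5.

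**3. Power of the unadjusted t-test, 18 per arm.** Leaving out the covariate inflates the SD to √(1 + p(1−p)b²). The noncentrality is 0.60 × √(18/2) = 1.80, divided by that SD, on 34 degrees of freedom.

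| b (SD) | p | Inflated SD | Noncentrality | Power |
|---|---|---|---|---|
| 0 | any | 1.000 | 1.80 | 0.42 |
| 0.5 | 0.3 / 0.5 | 1.026 / 1.031 | 1.75 / 1.75 | 0.40 / 0.40 |
| 0.8 | 0.3 / 0.5 | 1.065 / 1.077 | 1.69 / 1.67 | 0.38 / 0.37 |
| 1.2 | 0.3 / 0.5 | 1.141 / 1.166 | 1.58 / 1.54 | 0.33 / 0.32 |

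A simulation of 40,000 two-arm comparisons per setting agrees: 0.41–0.42, 0.39–0.40, about 0.37 and 0.32–0.34. At p = 0.2 the same formula gives a smaller loss: 0.38 at 0.8 SD and 0.35 at 1.2 SD.

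**4. Power with adjustment.** In the same simulation, adding MEP status to the model keeps power at about 0.41 for every b. If b = 0 the covariate costs about one power point (0.416 to 0.406 at p = 0.3).

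**5. Type I error.** Averaged over allocations, the unadjusted test stays at 0.05. Given a gap of 30 points or more, it is about 0.08 at 0.5 SD, 0.11–0.12 at 0.8 SD and 0.19 at 1.2 SD. Such gaps occur in 4–7% of pairwise comparisons (p = 0.3 to 0.5).

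**6. Stratifying without adjusting.** At b = 0.8 SD, stratified allocation followed by the unadjusted t-test gives power of 0.36–0.37 and type I error of 0.035–0.038. Power is not recovered and the test becomes conservative. Stratified allocation with adjustment gives 0.42.

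**The case against.** - **The Discussion asks a question.** MEP absence is listed as unresolved, beside miniaturisation and cost-effectiveness, and the question concerns effect modification. This stands: MEP status is a suspected factor, and the article does not call it an established predictor.
- **The article addresses the matter elsewhere.** It plans a mechanistic substudy in the first 30 participants linking excitability profiles to response, and a correlation of MEP change with FMA-UE change. This is true, but neither adjusts the comparison between arms.
- **The tests may be meant for MEP data only.** The Statistical analysis section opens by naming MEP data. However, it goes on to count data and scales, and it gives no other method for comparing the arms on the clinical outcomes.
- **Allocation.** A reader might infer that the sequence is simple and unstratified, and hence that arm sizes will be unequal. The article does not say so. Strata and blocks are commonly left to the full protocol, and 1:1:1 with 18 per group fits restricted allocation equally well. That inference is not supported.
- **Imbalance deciding the result.** A reader might also infer that a chance imbalance could by itself produce a positive finding. Steps 2 and 5 do not support this: plausible gaps shift the contrast by a fraction of the design effect, and the unconditional error rate is intact.
- **The covariate cannot be used everywhere.** A participant without an MEP has no resting threshold, amplitude or latency, so MEP status coincides with whether those outcomes exist. This stands and limits the fix to the clinical outcomes.
- **Choice of covariate is partly preference.** This is fair in general, but here the protocol itself singles out this factor and already collects it.

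**Conclusion.** The point holds for the analysis. The stated between-arm tests for the clinical outcomes leave out a baseline factor that the protocol suspects of governing benefit and has in hand before allocation. It is an improvement to a valid method, and the tests as stated are not biased on average.

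The size depends wholly on assumed values. For 30–50% MEP-absent, the loss is about 4 power points at an effect of 0.8 SD and 7–9 points at 1.2 SD, from a base near 0.41 for d = 0.60. There is no loss if MEP status is not prognostic. Adjustment also protects the estimate in the minority of allocations with a large gap. It does not by itself answer whether absent MEPs preclude benefit, which needs the arm contrasts by MEP status.

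**What to change.** Replace the unadjusted between-arm tests for the clinical outcomes with a prespecified model that includes baseline MEP presence (present or absent) in the paretic abductor pollicis brevis. Use a linear model for FMA-UE, ARAT and the Modified Barthel Index, and a suitable ordinal model for MAS. Define presence in advance, for example by whether the article's own resting-threshold criterion can be met. Report arm contrasts by MEP status as exploratory. Do not apply this covariate to MEP amplitude or latency.

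If the allocation list has not yet been made, stratifying by MEP status is optional, and useful only together with the adjustment. If allocation has begun, keep the list and change the analysis alone.

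The cost is one degree of freedom, about one power point if MEP status turns out not to matter, and a fitted model in place of simple tests. No new measurement is needed. Stratification would also require the MEP result before the envelope is drawn.

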### Inclusion and exclusion criteria

We will recruit adults aged 40–80 years who sustained their first-ever unilateral ischemic or hemorrhagic stroke 3–12 months earlier, as confirmed by Computed Tomography/Magnetic Resonance Imaging and classified according to World Health Organization or International Classification of Diseases criteria. Participants must present with moderate upper-limb —impairment defined as a MAS score ≥ 1 or a Fugl-Meyer Upper Extremity score between 20 and 50 and be able to understand and follow single-step verbal instructions. All subjects must sign written informed consent. Individuals will be excluded if they have epilepsy, intracranial hypertension, or any implanted metal devices; unstable medical conditions such as severe arrhythmia, acute infection, or hepatic/renal failure; pregnancy or lactation; recent (past 3 months) craniotomy, botulinum-toxin injections, or high-dose centrally acting antispasmodics; unhealed fractures, severe arthritis, or skin lesions in the upper limbs; cognitive impairment (Mini-Mental State Examination < 24) or severe psychiatric illness/substance abuse; or previous intolerance to magnetic stimulation (Table 2).

**Table 2 T2:** Inclusion and exclusion criteria.

**Inclusion criteria**	**Exclusion criteria**
Aged 40–80 years	History of epilepsy or intracranial hypertension
First-ever unilateral ischemic or hemorrhagic stroke, 3–12 months post-stroke	Any implanted metal devices (e.g., pacemaker, cochlear implant)
MAS score ≥ 1 in the affected upper limb	Unstable medical conditions (e.g., severe arrhythmia, acute infection, hepatic/renal failure)
FMA-UE score between 20 and 50	Pregnancy or lactation
Able to understand and follow single-step verbal instructions	Botulinum toxin injection in the affected upper limb within the past 3 months or recent craniotomy
Provides written informed consent	Unhealed fractures, severe arthritis, or skin lesions in the upper limbs
	Cognitive impairment (MMSE < 24) or severe psychiatric illness/substance abuse
	Known previous intolerance to magnetic stimulation

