**Methods:**

This single-center, three-arm, sham-controlled, single-blind randomized controlled trial enrolled 54 stroke survivors (aged 40–80, 3–12 months post-stroke, Modified Ashworth Scale score ≥1). Participants were randomized in a 1:1:1 ratio to receive a 10-session intervention over 2 weeks (5 days/week). Each session consisted of stimulation followed by 30 min of conventional physical therapy. The stimulation protocols were: Group 1: active iTBS over extensor carpi radialis longus + sham cTBS over flexor carpi radialis; Group 2: sham iTBS + active cTBS; Group 3: active iTBS + active cTBS. Stimulation was delivered using a MagTD stimulator at 110%−120% of the peripheral motor threshold (mean 38.4% maximum stimulator output), with 600 pulses per session (50 Hz burst frequency, 5 Hz theta rhythm).

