The MAS is the gold-standard instrument for quantifying spasticity. For the upper limb it demonstrates good reliability: inter-rater ICC = 0.781 (95% CI 0.679–0.853), κ = 0.625 (95% CI 0.350–0.801); intra-rater ICC = 0.748 (95% CI 0.671–0.809), κ = 0.593 (95% CI 0.467–0.696) (17). Scores range from 0 (normal tone) to 4 (severe spasticity preventing joint movement), with an additional 1+ grade for mild spasticity. In this study, the same blinded assessor will evaluate the spastic FCR at baseline, immediately after the last session, and at the 2-week follow-up: the elbow is flexed 90 °, the forearm is in neutral, and the wrist is passively extended at ≈1 rad/s; a sustained decrease of ≥1 point is considered a clinically meaningful improvement.

The FMA-UE is a specialized scale designed to evaluate upper limb motor function in stroke patients. The estimated range of its clinically important difference is 4.25–7.25 points (22). It consists of 33 items, covering movements of both the proximal and distal parts of the upper limb. The total score ranges from 0 to 66 points, with each item scored from 0 points (inability to complete the action, accompanied by severe abnormal movements) to 2 points (the action is performed in a standardized way and can be completed smoothly).

The ARAT is a standardized scale used to assess the upper limb motor function of patients with neurological impairments. It has high reliability and internal validity, with an intra-class correlation coefficient ranging from 0.992 to 0.998 (23). The scale consists of 19 assessment items, with a total score of 57 points. The score for each item ranges from 0 points (poor upper limb function, unable to complete the action) to 3 points (good upper limb function, the action is standard and completed smoothly).

The Modified Barthel Index is a widely used standardized scale in clinical practice for assessing activities of daily living. It evaluates an individual's basic daily living abilities, covering 10 items such as feeding, bathing, grooming, dressing, bowel and bladder control, toilet use, transfers, ambulation or wheelchair mobility, and stair climbing. It has good reliability and internal validity, with an intraclass correlation coefficient of 0.95 (24, 25). The scale consists of 10 assessment items, with a total score ranging from 0 (completely dependent on others) to 100 (completely independent), effectively reflecting an individual's degree of self-care in daily life.

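### The eligibility text accepts MAS ≥ 1 or FMA-UE 20–50, Table 2 lists both, and neither ties the MAS criterion to the wrist flexor that is treated and scored

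*Protocol article*

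**What the plan says.** Three places in the protocol article state who may enter, and a fourth states what is scored.

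- **Inclusion and exclusion criteria, running text.** Moderate impairment is "defined as a MAS score ≥ 1 or a Fugl-Meyer Upper Extremity score between 20 and 50". Either condition alone is enough.
- **Table 2.** One row reads "MAS score ≥ 1 in the affected upper limb" and the next reads "FMA-UE score between 20 and 50". They stand beside age, stroke history and consent, and neither is marked as an alternative to the other.
- **Abstract, Methods.** Participants are described as "aged 40–80, 3–12 months post-stroke, Modified Ashworth Scale score ≥1". No FMA-UE range appears.
- **Outcome measures.** For the MAS, "the same blinded assessor will evaluate the spastic FCR at baseline, immediately after the last session, and at the 2-week follow-up". On the scale itself: "Scores range from 0 (normal tone) to 4". A sustained fall of at least 1 point counts as clinically meaningful.

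The stimulation section directs active or sham cTBS to the spastic muscle, the FCR, in all three groups. Table 1 schedules the MAS at screening, but the FMA-UE only from T0, the column in which randomization falls.

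The exclusions also appear twice. The text excludes "recent (past 3 months) craniotomy, botulinum-toxin injections, or high-dose centrally acting antispasmodics". Table 2 has no antispasmodic row, gives craniotomy no time window, and limits botulinum toxin to the affected upper limb.

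**The concern.** Eligibility decides who is randomized and whom the result describes. Two screeners, one working from the text and one from Table 2, would enrol different people.

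The difference matters most for the MAS. The intervention rests on an imbalance between a spastic flexor and its antagonist. A participant without spasticity in the FCR has no such target, and their MAS has no room to fall. The abstract's hypothesis for spasticity is a MAS decrease of at least 1, which such a participant cannot reach in any arm. Analysis cannot later restore the intended population among those randomized.

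**Working it through.** No figure in the article depends on this point, so there is none to reproduce. The check applies each stated rule to four example patients.

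| Example patient | Running text | Table 2 (rows read jointly) | Abstract |
|---|---|---|---|
| MAS 0 throughout the limb, FMA-UE 30 | eligible | not eligible | not eligible |
| FCR MAS 1, FMA-UE 60 | eligible | not eligible | eligible as far as stated |
| Elbow MAS 1, FCR MAS 0, FMA-UE 30 | eligible | eligible | eligible as far as stated |
| FCR MAS 1, FMA-UE 30 | eligible | eligible | eligible |

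Table 2 does not print the word 'and'. Reading its rows as jointly required is the usual convention, and the age, stroke and consent rows can be read in no other way.

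Two results follow. First, the text and Table 2 disagree on the first two patients. Second, all three places admit the third patient, so changing 'or' to 'and' is not enough by itself.

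**Effect on the MAS contrast.** Let q be the share of participants with FCR MAS 0 at baseline. The documents do not give q, so it is an assumption here. Suppose q is the same in each arm and no between-arm MAS difference arises among these participants. If Δ is the mean contrast among the rest, then

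contrast in everyone = (1 − q) × Δ + q × 0 = (1 − q) × Δ.

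| Assumed q | Expected number of 54 at the floor | Contrast remaining |
|---|---|---|
| 10% | 54 × 0.10 = 5.4 | 0.90 Δ |
| 20% | 54 × 0.20 = 10.8 | 0.80 Δ |
| 30% | 54 × 0.30 = 16.2 | 0.70 Δ |

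The same shrinkage holds in SD units only if the SD is unchanged. A group fixed at zero change would alter the SD too, so the table shows direction and rough scale only.

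**The case against.** The strongest reply is that the 'or' is a drafting slip. The abstract and Table 2 both state MAS ≥ 1. Table 1 measures the MAS at screening. The stimulation and outcome sections take a spastic FCR for granted in every participant. The full protocol, which a journal article condenses, may name the joint. Much of this stands: it makes an internal inconsistency more likely than a deliberate choice to enrol people without spasticity. It does not remove the point, because both rules are printed in the same section and only one can be followed.

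Three stronger readings are tempting and are not supported.

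- *Every contrast is diluted.* A reader might infer this, but a MAS floor limits only the MAS. A person with MAS 0 and FMA-UE 30 can still change on FMA-UE, ARAT, the Modified Barthel Index and MEPs, and the stated primary objectives include function and neurophysiology.
- *The loss of power can be calculated.* It cannot. The share q is not given. The only effect size available, d = 0.60 in the sample-size section, concerns iTBS and upper-limb motor improvement, not the MAS. The SD among mixed participants is unknown.
- *A planned responder analysis is compromised.* The 1-point fall appears as a threshold of clinical meaning and as a hypothesis. The statistical analysis section describes no MAS responder analysis.

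The missing antispasmodic row is also a smaller matter than it may look, because the exclusion is stated in the text and the table is a summary.

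**Conclusion.** The contradiction between the text on one side and Table 2 and the abstract on the other is established by the wording alone. So is the gap between a MAS criterion for the whole limb and an outcome scored on the FCR. The consequence is confined to the MAS contrast, which is diluted if any participant enters with FCR MAS 0. By how much is unknown; a 10–30% shrinkage corresponds to an assumed q of 10–30%, equal across arms and with the SD unchanged.

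The documents do not show that anyone without spasticity has been enrolled. This is an internal inconsistency that should be corrected. Its importance rests on who is eligible and on whether the MAS question can be answered in them, not on any power calculation.

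**What to change.** 1. In the running text, replace 'or' with 'and', so that it agrees with Table 2 and with the abstract's MAS requirement.
2. In the text and in Table 2, state that MAS ≥ 1 applies to the wrist flexors (FCR), the muscle treated and scored.
3. Show the FMA-UE at screening in Table 1. It becomes mandatory for entry under step 1 but is first scheduled at T0.
4. Reconcile the exclusion lists in the text and Table 2 on three items: antispasmodics, the craniotomy window, and whether the botulinum-toxin exclusion is limited to the affected upper limb. Which version applies is for the investigators to decide.
5. If anyone has already entered under 'or', keep them in the main analysis as randomized, and pre-specify a supporting MAS analysis in those with baseline wrist MAS ≥ 1.

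The cost is a wording amendment, one more assessment at screening, and a slightly narrower recruitment pool.
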